### Subject Population(s) for Analysis

The population that will be included in the primary study analysis will include subjects who were randomized into the study and who completed FIT as an intention to treat analysis. ~~Two populations will be included in the secondary analysis. The first will include any subjects randomly selected to receive a subsample questionnaire and who completed the questionnaire. The second will include patients who currently receive FIT as standard of care in the Penn Family Care Clinic. In order to provide a comparison group, retrospective chart review will be performed on this group in order to compare response rates and demographics between study participants and the eligible clinic population. The data collected on these patients will be identical to the data collected on study participants (i.e. demographics, inclusion criteria, exclusion criteria, response rates).~~

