## 2. Objectives

Primary Objective is to assess the effectiveness of financial incentives to increase the response rates to mailed FIT.

Secondary Objective is to further our understanding of the impact of financial incentives on completing mailed FIT.

Primary Study Endpoint ~~will be an increase in~~ **is the** return rate of completed FITs **within 2 months of outreach between the intervention arms when compared to the control arm.**

Secondary Study Endpoints ~~n/a (the secondary objective is qualitative in nature and thus there is no quantitative endpoint)~~ **include the return rate of completed FITs within 6 months of outreach, the percentage of FIT results that are positive, and the percentage of those positive subjects that receive diagnostic colonoscopy. We will look at rates of participation in FIT or colonoscopy that occur outside the study setting during the study period as an exploratory outcome. We will also evaluate the results of the qualitative survey.**

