**\*\*New changes from initial protocol notated in bold, parts removed from initial protocol notated in strikethrough**

### Power and Sample Size

Through the PFC quality improvement initiative, we have found the accuracy rate of the EMR algorithm to be approximately 80%. As such, we anticipate 1,080 of 1,350 subjects will be eligible **and randomized**, with 270 subjects enrolled on to each of the four arms in a 1:1:1:1 ratio. We estimate a base return rate for controls to be 15% ~~and a base return rate for the intervention arms to be 25%. We will compare the intervention arms against the control arms but we will not compare one intervention against another intervention.~~ **We will compare each intervention arm to the control and use Bonferroni correction for an alpha of .017 (.05/3) in order to account for three comparisons.** Thus, we have 80% power to detect an absolute ~~40%~~ **11 percentage point** increase in response rate using a two-sided Type 1 error rate of ~~0.05~~ **0.017**.

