### Data Analysis

We will conduct a chi-square analysis using statistical software Stata 12 to compare each intervention arm to the control arm. ~~A second chi-square analysis will be performed by blinded members of the research team to compare response rates of the study participants and patients receiving FIT as standard clinical care.~~ Analysis will be conducted by the research team twelve weeks after the last subsample questionnaire is completed.

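### The sentence defining the primary analysis population contradicts itself: it makes completing FIT, the primary outcome, a condition of entry and calls the result intention to treat

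*Supplement*

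**What the plan says.** The current text defines the primary analysis population in one sentence. It appears in identical words in the final protocol (section 7, Subject Population(s) for Analysis) and in the final SAP (same heading): the population "will include subjects who were randomized into the study and who completed FIT as an intention to treat analysis". The text that follows it, on secondary populations, is struck out in both documents; this sentence is not.

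The related parts of the plan are:

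- **Primary endpoint** (final protocol, section 2, Objectives): the return rate of completed FITs "within 2 months of outreach between the intervention arms when compared to the control arm".
- **A later window** (same section): a secondary endpoint is the "return rate of completed FITs within 6 months of outreach".
- **Test** (Data Analysis): "We will conduct a chi-square analysis using statistical software Stata 12 to compare each intervention arm to the control arm".
- **Sample size** (Power and Sample Size): "270 subjects enrolled on to each of the four arms in a 1:1:1:1 ratio", a control return rate of 15%, 80% power for an "11 percentage point" increase, and the instruction to "use Bonferroni correction for an alpha of .017 (.05/3) in order to account for three comparisons".
- **Leaving the study after randomization** (final protocol, section 6, Subject Withdrawal): subjects may ask to be withdrawn, and the investigator may discontinue them, for example on self-report of earlier guideline-concordant screening. Neither document says whether such subjects stay in the denominator.

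**The concern.** The sentence joins two conditions, randomized and completed FIT, and then labels the set intention to treat. The two halves are incompatible. An intention-to-treat denominator is fixed at randomization. The second condition is met only by subjects who have the outcome.

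What is at stake is the trial's main question, whether an incentive raises the proportion who return a kit. Non-returners carry half of that information. Any rule that removes them, wholly or in part, replaces the randomized comparison with one among subjects selected by a behavior that the incentive is meant to change. With no other definition to fall back on, the plan also has no rule for the harder cases, such as a non-returner who reports earlier screening after the kit was mailed.

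**Working it through.** **Inputs.** From Power and Sample Size: n = 270 per arm (1,080 in total), control rate p1 = 0.15, detectable increase 0.11 and hence p2 = 0.26, two-sided alpha 0.017, stated power 80%. From Objectives: the primary window is 2 months and the secondary window is 6 months.

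**Step 1. Reproduce the stated power with all randomized subjects in the denominator.** I use the normal approximation with pooled variance under the null.

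- Mean rate: (0.15 + 0.26)/2 = 0.205.
- Standard error under the null: √(2 × 0.205 × 0.795 / 270) = 0.03475.
- Standard error under the alternative: √((0.15 × 0.85 + 0.26 × 0.74) / 270) = 0.03442.
- Critical value for alpha 0.017, two-sided: 2.387.
- Power = Φ((0.11 − 2.387 × 0.03475) / 0.03442) = Φ(0.787) = 0.784.

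The detectable difference at exactly 80% power is 11.2 points, which rounds to the stated 11. The plan's figure is therefore reproduced to within 2 points, with all 270 subjects per arm as the denominator.

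**Step 2. Apply the completion condition with the same 2-month window.** Expected completers are:

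- Control: 0.15 × 270 = 40.5.
- An incentive arm at 26%: 0.26 × 270 = 70.2.
- All four arms, *assuming* that each incentive arm reaches 26%: 40.5 + 3 × 70.2 = 251.1, or about 251 of 1,080.

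Every member of this set has returned a kit, so control against one incentive arm is 40/40 against 70/70.

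| | Returned | Not returned |
|---|---|---|
| Control | 40 | 0 |
| Incentive | 70 | 0 |

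The non-return column is empty and its expected counts are zero. The chi-square statistic divides by those counts, so it is undefined.

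**Step 3. The same returns over all randomized subjects.**

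| | Returned | Not returned | Total |
|---|---|---|---|
| Control | 40 | 230 | 270 |
| Incentive | 70 | 200 | 270 |

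Chi-square = 540 × (40 × 200 − 70 × 230)² / (270 × 270 × 110 × 430) = 10.27, p = 0.0013, below 0.017. The planned test works.

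**Step 4. Read completion as return at any time up to 6 months.** The sentence gives no window, so this reading is open. Let R2 and R6 be an arm's return rates by 2 and by 6 months over all randomized subjects. The rate in the completers-only set is then R2/R6, the share of completers who were prompt. It can be below 100% and can differ between arms, so a test can be computed. It does not estimate the difference in R2. If an incentive raised R2 and R6 in the same proportion, R2/R6 would be equal in both arms and the analysis would show no effect although more kits came back. The set is also selected on a post-randomization outcome, so randomization no longer protects the comparison.

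**The case against.** The strongest reply is that nobody would carry out the literal sentence. It names intention to treat; the endpoint is a return rate; a chi-square between arms needs non-returners; and 270 per arm with a 15% control rate has meaning only over everyone randomized. Step 1 supports this. An analyst who tried the completers-only table would see an empty column at once and fall back on the intention-to-treat label.

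Most of this stands. A reader might infer from the sentence that the plan is settled on analyzing completers only and that the comparison therefore cannot be made. The documents do not support that: the same sentence and the power statement point to all randomized subjects, and nothing shows that completers alone would be analyzed. Nor does it follow without condition that every arm would show 100%. That holds only if completion carries the 2-month window, which the sentence does not say. The documents do not tie completion to 6 months either; that window belongs to a secondary endpoint and to the chart audit.

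The reply does not remove the need for a correction. Probable intent is not a definition, and the contradictory sentence is the only one available. The degenerate table would be noticed; quieter departures might not be. The protocol lets the investigator discontinue subjects who self-report earlier screening, and the exclusion criteria cover self-reported procedures. Reminders go only to subjects who have not returned a kit, so contact that might prompt such a report falls more on non-returners. Whether those subjects stay in the denominator is a practical question that the plan leaves open.

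**Conclusion.** The concern holds as an internal contradiction in the definition of the primary analysis population, present in the current text of both documents. The completion condition conflicts with the intention-to-treat label, with the endpoint and with the basis of the sample size. Applied with the 2-month window, it makes the primary test undefined; applied with a longer window, it gives a comparison of promptness among completers.

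The figure of about 251 of 1,080 is only an illustration. It rests on the plan's 15% control rate and on the assumption that all three incentive arms reach 26%. The final plan gives 11 points as a detectable difference and does not predict a rate for each arm. The conclusion does not depend on that figure. Because the sentence governs the primary analysis and nothing else in the current text overrides it, it should be corrected before the data are analyzed.

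**What to change.** Replace the sentence in the final protocol (section 7) and in the final SAP with:

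> *The primary analysis includes all randomized subjects (planned 270 per arm) in the arm to which they were assigned, including those later withdrawn or discontinued; subjects with no completed FIT returned within 2 months of outreach count as non-returners.*

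This settles three things together: the denominator, the window, and the handling of subjects who leave or are found ineligible after randomization.

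The cost is one sentence in each document. No new data are needed. Sample size and power are unchanged, because the stated calculation already uses all 270 per arm (about 0.78 in Step 1, against the stated 80%).

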## Summary of Statistical Analysis Plan Modifications

The analysis plan was updated to include the following modification of the power calculation:

We will compare each intervention arm to the control and use Bonferroni correction for an alpha of .017 ( $.05/3$ ) in order to account for three comparisons. Thus, we have 80% power to detect an absolute 10% 11 percentage point increase in response rate using a two-sided Type 1 error rate of 0.05 0.017.
